#### Masking

Researchers will be single blinded as to which arm families belong to including data analyses. Participating families and paediatric oncologists allocated to the intervention group, and ACP facilitators, cannot be blinded, as they will actively participate in some part of the program. Participants in the control group will subsequently be informed about their group allocation. Research staff responsible for data analyses will not receive any information about a family’s group allocation.

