**Discussion:**

The BOOST pACP program has been developed to stimulate conversations on ACP themes between parent(s) and the adolescents, simultaneously lowering the threshold to discuss similar themes with healthcare professionals, initiating a process of normalization and integration of ACP in standard care. This combined outcome and process evaluation aims to contribute to building the necessary evidence to improve ACP in paediatric oncology.

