## Methods

### Study design

A multi-centre parallel-group randomised controlled superiority trial [25] (RCT) with embedded mixed-methods process evaluation, comparing the BOOST pACP program to standard care (control group). Adolescent patients and their parent(s) will be randomised with a 1:1 allocation ratio to the intervention arm or the control arm after baseline assessment. The mixed-methods process evaluation is structured according to the Medical Research Council (MRC) Framework by Moore et al. [26].

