### Study setting and population

The study will take place in four participating university hospitals in Flanders, Belgium. Families in the intervention group have the choice of having the ACP conversations and visits from the data collector at home, in the hospital or online due to COVID-19 measures. The BOOST pACP program is targeted at adolescents, their parent(s) and involved paediatric oncologists. Inclusion- and exclusion criteria can be found in Table 1. Adolescents should be age 10–18, diagnosed with any type of cancer at any stage and currently receiving (active) oncology treatment. ‘Active treatment’ encompasses adolescents: 1) who are currently receiving treatment; 2) for whom treatment is planned; 3) for whom the last treatment took place maximally 3 months ago.

**Table 1 Tab1:** Inclusion and exclusion criteria of adolescents, parent(s) and paediatric oncologists

Inclusion criteria (combined by ‘AND’)	Exclusion criteria (combined by ‘OR’)
*Adolescent*	
Aged between 10 and 18 years	Participated in the feasibility test
Diagnosis of cancer ≥3 months prior to inclusion	Intellectual disabilities to an extent that general communication is very difficult, or serious mental health problems to an extent that the extra effort of participating in the study is not justified (estimated by the paediatric oncologist and psychologist)
Aware of, or informed about, cancer diagnosis according to parent(s)	Life expectancy ≤3 months
Receiving active treatment in a paediatric oncology ward	Not receiving active treatment (last treatment was more than 3 months ago)
Fluent Dutch language understanding	
*Parent(s)*	
Aware of, or informed about the diagnosis of their child according to the clinician	Participated in the feasibility test
Fluent Dutch language understanding	Intellectual disabilities to an extent that general communication is very difficult, or serious mental health problems to an extent that the extra effort of participating in the study is not justified (estimated by the paediatric oncologist and psychologist)
*Paediatric oncologist*	
Medically involved in the treatment of the adolescent, indicated by the family to be the oncologist with whom the family has most contact about treatment	
Fluent Dutch language understanding	

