**Secondary endpoints**						
2. Quality of Parent-Adolescent Communication	PACS	20 items	Adolescent	x		x
3. Attitude on talking with the other (parent(s)/ their child) about what the adolescent finds important regarding his/her care and treatment	Created by the research team^a^	8 items	Adolescent	x	x	x
		7 items	Parent(s)	x	x	x
4. Self-efficacy towards talking with the other (parent(s)/ their child) about different ACP themes	Created by the research team^a^	9 items	Adolescent	x	x	x
4a. if the child initiates the conversation	Created by the research team^a^	9 items	Parent(s)	x	x	x
4b. to initiate the conversation his/herself	Created by the research team^a^	9 items	Parent(s)	x	x	x
5. Self-efficacy towards talking with their child and letting their child talk in different situations	Created by the research team^a^	6 items	Parent(s)	x	x	x
6. Behaviour: talking with the other (parent(s)/ their child) about different ACP themes	Created by the research team^a^	9 items	Adolescent	x	x	x
		9 items	Parent(s)	x	x	x
7. Intention to talk with the other (parent(s)/ their child) parent(s) about different ACP themes	Created by the research team^a^	9 items	Adolescent	x	x	x
		9 items	Parent(s)	x	x	x
8. Behaviour: talking with paediatric oncologist about different ACP themes	Created by the research team^a^	9 items	Adolescent	x	x	x
9. Intention to talk with paediatric oncologist about different ACP themes	Created by the research team^a^	9 items	Adolescent	x	x	x
10. Anxiety	PROMIS Anxiety 8a Short version [33]^b^	8 items	Adolescent	x	x	x
	PROMIS 7a Short version [34]^b^	7 items	Parent(s)	x	x	x
11. Level of shared decision making	CollaboRATE Scale [35, 36]^c^	3 items	Parent(s)	x	x	x
12. Satisfaction items for the intervention group	Created by the research team	14 items	Adolescent and parent(s)		x	x
13. Behaviour & intention to discuss ACP with the family	Created by the research team	3 items	Oncologist	x	x	x
14. Quality of Life	EQ-5D-Y [37]	6 items	Adolescent	x	x	x

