#### Secondary hypotheses testing

All secondary endpoints will be evaluated by testing the BOOST pACP program against the control group for each participant population separately (adolescents, parents and paediatric oncologists) with random effects being hospital and line of treatment.

For each of the primary and secondary endpoints, subgroup analyses will be performed using formal interaction tests to explore the extent to which the outcomes of the trial differ by gender, working situation and family situation of the parent(s) and gender and prognosis of the adolescent. Interaction terms between gender, working situation and family situation of the parent(s) and gender and prognosis of the adolescent on the one hand and the trial arms on the other hand will be added to the analysis models.

By including the baseline measurement as a predictor variable pre-existing differences will be controlled, enhancing the sensitivity of the analyses. Alpha is set at 0.05. To interpret the magnitude of the effects for the different outcomes, we will estimate effect sizes (Cohen’s d). Analyses will be conducted in IBM SPSS and R.

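### The oncologist endpoint (Table 3, item 13) ignores that one oncologist may report on families in both arms: the model has no oncologist effect, and control reports may be contaminated

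*Protocol article*

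**What the plan says.** The Study design section randomises families: "Adolescent patients and their parent(s) will be randomised with a 1:1 allocation ratio to the intervention arm or the control arm after baseline assessment". The Allocation section stratifies by age only, and no procedure allocates an oncologist. In Table 1 (Study setting and population) an oncologist enters by being "indicated by the family to be the oncologist with whom the family has most contact about treatment".

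The Masking section nevertheless refers to oncologists as allocated: "Participating families and paediatric oncologists allocated to the intervention group, and ACP facilitators, cannot be blinded". Table 3 lists "13. Behaviour & intention to discuss ACP with the family" at T0, T1 and T2 with the oncologist in the unit-of-analysis column. The Secondary hypotheses testing section compares BOOST with control "for each participant population separately (adolescents, parents and paediatric oncologists) with random effects being hospital and line of treatment".

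The oncologist is also exposed to the programme. The Study setting section names involved oncologists among its targets. In Table 2 (item 4, activities 16 and 17) the facilitator, if the family permits, briefs the oncologist on the conversations and asks for the summary sheet to be filed. The Discussion part of the abstract describes the programme as "initiating a process of normalization and integration of ACP in standard care".

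Under Data collection procedures and Data management, the oncologist's questionnaire is about one adolescent and carries that adolescent's code.

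**The concern.** If oncologists are a population with arms, an oncologist named by one intervention family and one control family fits in neither. If the unit is instead one report per family, the arm is clear, but two things in the stated analysis need attention.

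First, an oncologist's reports on several families share that person's habits and response style. A hospital effect captures only what colleagues in the same hospital have in common.

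Second, the transfer of information acts on the same person who later reports on control families. If a briefing changes how that oncologist approaches other patients, the control condition drifts towards the intervention, and the plan does not mention this. A null result on item 13 could then be read as no effect on oncologists when part of the explanation is a changed comparator.

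**Working it through.** **1. The plan's own figure.** The only sample size is for the primary endpoint: difference 7, SD 11.4, alpha 0.05, power 80%. A two-sided two-sample t-test gives 42.6, so 43 per arm, and 86 / 0.9 = 95.6, so 96 families. The stated figures reproduce. No sample size is given for item 13, and nothing below changes the primary calculation.

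**2. How likely is it that one oncologist serves both arms?** Inputs from the protocol: 96 families, 1:1 (48/48), four hospitals, no stratification by oncologist. Assumption: m families per oncologist, equal for all, because the number of oncologists is not given.

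P(both arms) = 1 − 2 × C(96−m, 48) / C(96, 48)

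| Families per oncologist (m) | Oncologists (96/m) | P(both arms) |
|---|---|---|
| 2 | 48 | 51% |
| 3 | 32 | 76% |
| 4 | 24 | 88% |
| 6 | 16 | 97% |

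Overlap is therefore likely over a wide range, but it is inferred from the design and not stated.

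**3. What does the missing oncologist effect do?** Let ρ be the correlation between two reports by one oncologist beyond that shared within the hospital, and σ² the report variance.
- One report in each arm: the difference has variance 2σ²(1−ρ), but a model without an oncologist term works with 2σ². Its standard error is too large.
- All m reports in one arm: their mean has variance (σ²/m)[1 + (m−1)ρ], but the model works with σ²/m. Its standard error is too small.

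From step 2 the first case should predominate unless caseloads are very small. The consequence is then mainly lost precision, not inflated false positives.

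**4. How many control reports could follow a briefing?** Assumptions: entry uniform over the 24-month recruitment period; transfer 2.5 months after entry (Table 2 gives three months from booklets to transfer); each other family of that oncologist is in the intervention arm with probability 0.5; a proportion p of intervention families permits transfer. For a control family entering at month t, reporting at t+3 (T1) or t+7 (T2), another family's transfer comes first if that family entered before t+h, with h = 3 − 2.5 = 0.5 or h = 7 − 2.5 = 4.5.

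Share = 1 − mean over t of [1 − (p/2) × min(1, (t+h)/24)]^(m−1)

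| m | T1, p = 1 | T2, p = 1 | T1, p = 0.5 | T2, p = 0.5 |
|---|---|---|---|---|
| 2 | 26% | 33% | 13% | 17% |
| 3 | 43% | 54% | 24% | 30% |
| 4 | 55% | 67% | 33% | 41% |
| 6 | 69% | 82% | 47% | 57% |

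With p = 0.7 and m = 3, 4, 6, the T2 shares are 41%, 53% and 70%.

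**5. From exposure to bias.** If a fraction f of the effect carries over to later control reports, the contrast shrinks by f × share. Taking f = 0.5 purely for illustration and m = 3 to 6: with p = 1, by 22–35% at T1 and 27–41% at T2; with p = 0.5, by 12–23% at T1 and 15–29% at T2. With f = 0 there is no bias. The protocol gives no value for f, p or m.

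**The case against.** A reader might infer that an oncologist cannot be placed in either arm, so that the comparison is undefined. The document does not support that. The questionnaire is about one adolescent and bears that adolescent's code, so each report inherits a randomised arm. The unit column in Table 3 seems to name the respondent: it also says oncologist for item 16, the disease and treatment information about the adolescent. The Masking phrase reads most naturally as loose wording for the oncologists of intervention families. This part of the defence stands.

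A reader might also infer that control oncologists are known to be progressively exposed and that the contrast is diluted by a definite amount. That too goes beyond the text. Overlap is inferred, transfer depends on family permission, and a summary of one family's conversations is not ACP training. The percentages in steps 4 and 5 show how the answer moves with the assumptions; they are not estimates.

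Two further points stand. The hospital effect already absorbs some of the correlation, so reports are not treated as wholly unrelated. And item 13 is one three-item secondary endpoint, with no oncologist outcome in the Objectives section.

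None of this supplies an oncologist term in a model whose random effects are stated, or any acknowledgement that control reports may be contaminated.

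**Conclusion.** The concern holds in a limited form. The report-level comparison by the family's arm is valid in definition, but the stated model omits a likely source of clustering, and the plan does not address possible contamination of control reports. The first misstates standard errors, mostly at the expense of precision, provided that most oncologists serve both arms (about 51% to 97% at 2 to 6 families each, under equal caseloads). The second would bias item 13 towards no effect, by an amount that cannot be determined from the document. The primary endpoint and the 96-family sample size are untouched. The changes are cheap and worth making before analysis.

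**What to change.** 1. In the Masking section, refer to oncologists of families allocated to the intervention.
2. For item 13, define the unit as one oncologist's report on one randomised family, with the family's arm.
3. Add a random intercept for oncologist to the stated model, using a pseudonymous oncologist code. The data collectors know who receives each questionnaire.
4. As an exploratory analysis only, examine prior exposure: the number of transfers the oncologist had received for other families before the report. Exclude the family's own transfer, since counting it would absorb part of the effect under study. Apply the count in both arms and adjust for calendar time. Do not simply drop later control reports, because that would confound arm with calendar time. Someone outside the analysis team should prepare the variable so that analysts stay blinded.
5. State that a null result on this endpoint may reflect contamination.

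The cost is one more variance component, which may be poorly estimated if most oncologists have few families; one code in the dataset; and a little extra analysis. Transfer dates must be available: the facilitator diary is meant to cover all activities but is described as completed after conversation sessions, so confirm that the transfer date is recorded. No extra families, visits or questionnaires are needed.

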### Data collection procedures

Quantitative data is collected at baseline (T0), after 3 months (T1), and after 7 months (T2) (see Fig. 3), using self-reported questionnaires that are pseudonymized using individual identifier codes attributed by the data collector. During a home visit, the data collector will gather written consent from both parents and written assent from the adolescent, immediately after which the baseline questionnaire is provided to the participant (paper-pencil or online using ‘LimeSurvey’, depending on the choice of the participant). The data collector will fill out the questionnaire together with the adolescent in an interview format. This will be done in a separate room from the parent(s), to avoid that the adolescent is being influenced by their presence. Parent(s) can either choose to fill out their questionnaire independently at the same time or later. The paediatric oncologist mentioned by the family as the one with whom they have most contact about care and treatment will receive a baseline questionnaire about the adolescent via an e-mail link. The data collector will send out one reminder to the parents and paediatric oncologist after 1 week. Data collection procedures are repeated at T1. At T2, questionnaires are sent to parents and adolescents, either online or via postal mail. To reduce loss to follow-up, improve retention, and encourage adolescents to fill out the questionnaires, retention gifts will be provided after completion of each data collection, at T0, T1 and T2.

Data collection procedures for the process evaluation (Additional file 2), include:
structured diary filled out by facilitators: the facilitators keep track of all activities they perform regarding the BOOST pACP program by filling out a structured diary, including multiple choice and open-ended questions, after each BOOST pACP conversation session. The diary will be completed in a Word template and will be stored in a secure folder.semi-structured individual interviews with facilitators; both facilitators will be interviewed for 60 min by a researcher at 6 months, 12 months, 18 months and after the end of the data collection period at 24 months.semi-structured individual interviews with a variety of involved paediatric oncology teams after 12 months and after study completion, at 24 months.each BOOST pACP conversation is recorded by audio (after informed consent of participants).

All interviews are structured according to a pre-specified topic list and audio-taped for analysis purposes.

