4.	WHAT Procedures (each of the procedures, activities, and/or processes used in the intervention, including any enabling or support activities)	The BOOST program entails 10 program components that can be carried out via 17 activities: **As part of “Facilitator training (including manual)” component (1)** Activity 1: Selection of two external facilitators Activity 2: Preparation of facilitators for the training Activity 3: Two-and-a-half-day training program for facilitators Activity 4: Intervision sessions (discussing challenges in case studies) approximately every 4 months for facilitators (2–5 h) **As part of “Preparation booklets” component (2)** Activity 5: Data collectors give preparation booklets to the families that are assigned to the intervention group Activity 6: Adolescent and parent(s) read their preparation booklet before conversation session 1 takes place **As part of “Video” component (3)** Activity 7: The facilitator introduces the videos that will be shown in conversation session 1. Activity 8: Adolescent and parent(s) watch the video during conversation session 1. Activity 9: The facilitator asks whether the adolescent and parent(s) recognize any aspect from the video. **As part of “Conversation session 1” (4)** Activity 10: The facilitator guides the conversation session and introduces the conversation cards to the adolescent and parent(s): **As part of “Conversation session 2a” (5)** Activity 11: The facilitator guides the conversation session with the adolescent alone and uses conversation cards to discuss ACP themes. **As part of “Conversation session 2b” (6)** Activity 12: The facilitator guides the conversation session with the parent(s) alone and uses conversation cards to discuss ACP themes. **As part of “Conversation session 3” (7)** Activity 13: The facilitator guides the conversation session with the adolescent and parent(s) and allows them to discuss ACP themes. **As part of “Summary sheet” (8)** Activity 14: The facilitator introduces and explains the summary sheet. The facilitator asks whether the family would like the information they write down to be shared with the paediatric oncologist. **As part of “Conversation cards that can be used as a game of quartet at home” (9)** Activity 15: The facilitator explains the purpose of the quartet game and that the cards can facilitate communicating on ACP themes together at home in a playful way. **As part of “Transfer of information to a treating paediatric oncologist” (10)** Activity 16: In case the family gave permission, the facilitator makes an appointment with the paediatric oncologist that the family indicated. Activity 17: The facilitator gives a summary of the conversations with the family to the paediatric oncologist and asks whether the paediatric oncologist can add the summary sheet to the electronic dossier of the patient.

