### Allocation

Randomization will be performed after at least one of the parents has completed the baseline measurement. Block randomization with a 1:1 allocation ratio to either the intervention arm or the control arm will be performed, using a concealed envelope method. To ensure equal allocation of subgroups, we will stratify the allocation by age (10–14 years old vs 15–18 years old). We have opted for these age strata, because the cognitive development of adolescents between 10 and 14 years differs from those between 15 and 18 years [43, 44] which might influence the way they are able to talk about their care and treatment.Allocation concealment will be ensured, as the randomization service will not release the randomization code until the adolescent has been recruited into the trial, which takes place after all baseline measurements have been completed. After randomization, the data collector will then inform the families of their allocation to one of the study arms.

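### The primary PACS score at T1 is taken by interview by the data-collector role, which also discloses the allocation, and the Masking section does not mention that role

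*Protocol article*

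**What the plan says.** All references are to the protocol article.

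- **Endpoint.** Under Primary endpoint and Sample size, success rests on the adolescent's PACS score at 3 months (T1). The PACS is the adolescent's own rating of communication with the parents, on a 20 to 100 scale.
- **Mode.** Under Data collection procedures: "The data collector will fill out the questionnaire together with the adolescent in an interview format". This takes place in a room apart from the parents. The section then says: "Data collection procedures are repeated at T1". Only the last assessment differs: "At T2, questionnaires are sent to parents and adolescents, either online or via postal mail".
- **Who knows the arm.** Under Allocation: "After randomization, the data collector will then inform the families of their allocation to one of the study arms". In Table 2, item 4: "Data collectors give preparation booklets to the families that are assigned to the intervention group". The list of ten key components below Table 2 instead has the booklets sent to the family's home address. Table 3 lists 14 satisfaction items at T1 for the intervention group only.
- **Masking.** "Researchers will be single blinded as to which arm families belong to including data analyses". The section adds that the analysis staff receive no allocation information. It names as impossible to blind the families and oncologists in the intervention group, and the facilitators. It says nothing about data collectors.

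**The concern.** The primary outcome is a subjective rating given aloud. It is given to a member of the role that announced the arm and, by one of the two descriptions, handed over the intervention materials. An interviewer who knows that an adolescent has just completed a communication programme may probe, explain or record answers differently. The adolescent may also give that person more favourable answers. Both effects would probably favour the intervention, and both fall on the one score by which the trial is judged.

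Adjusting for the baseline PACS does not remove this. Baseline is taken before randomisation, so knowledge of the arm cannot affect it; at T1 it can. Blinding the analysts does not help either, because the distortion would already be in the recorded score. The authors accept that a person's presence can sway answers, since they separate the adolescent from the parents. They describe no matching safeguard against an interviewer who knows the arm.

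**Working it through.** **1. Tracing the role through the sections**

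| Step | Section | Who acts | Arm known to that role? |
|---|---|---|---|
| Baseline PACS | Data collection procedures | Data collector, by interview | No, before randomisation |
| Telling the family its arm | Allocation | Data collector | Yes |
| Booklets to intervention families | Table 2, item 4 (but posted, per the component list) | Data collectors | Yes |
| T1 PACS (primary) | Data collection procedures | Data collector, by interview | Yes for the role; no blinded assessor named |
| T2 PACS | Data collection procedures | Sent online or by post | No interview described |
| Data entry | Data monitoring | Data collectors | Yes for the role |

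The exposure is therefore present at T1, the primary time point.

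**2. Reproducing the plan's own figure**

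Inputs from Sample size: difference 7, SD 11.4, alpha 0.05 (two-sided assumed, as sidedness is not stated), power 80%, retention 90%.

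- The two-sample t-test needs 42.6 per arm, rounded up to 43, which is the stated figure. Power at 43 per arm is 0.804.
- Total: 2 × 43 = 86, and 86 / 0.90 = 95.6, rounded up to 96, which is the stated figure.

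The sample size is reproduced, and this point does not change it.

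**3. What a shift would do (illustration only)**

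The documents give no size for interviewer bias. I assume a between-arm shift s of 1 to 4 points. Over 20 items that is s / 20 = 0.05 to 0.20 points per item.

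Standard error of the difference: 11.4 × √(2/43) = 2.46.

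With no true effect, the two-sided rejection probability is that of a t-test with 84 degrees of freedom and noncentrality s / 2.46:

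| Assumed shift s | s / 2.46 | Share of the 7-point target (s / 7) | P(p < 0.05), no true effect |
|---|---|---|---|
| 0 | 0 | 0% | 5% |
| 1 | 0.41 | 14% | 6.9% |
| 2 | 0.81 | 29% | 12.7% |
| 3 | 1.22 | 43% | 22.6% |
| 4 | 1.63 | 57% | 36.3% |

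For scale, Sample size cites between-group PACS differences of 2.57 and 2.21 from two other intervention studies. A bias of 2 to 3 points would be as large as those effects.

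The planned model adjusts for baseline, whereas these rates do not. If baseline PACS predicts T1 PACS, the standard error falls and the same shift would be declared significant more often, so adjustment offers no protection.

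**The case against.** The strongest reply is that the trial cannot be blinded at the participant level. Adolescents know their arm and rate their own communication, so response bias would remain under self-completion or with a blinded interviewer. This stands. Only the increment added by the interviewer is avoidable, and its size is unknown. The table shows what a bias of a given size would do; it does not estimate what the interviewer adds.

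The interview also has merits: it keeps adolescents as young as 10 away from parental influence, and it gives T0 and T1 the same mode. That favours a fix that keeps the interview.

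Several stronger readings are tempting, but the documents do not support them:

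- **That the protocol claims blinded outcome assessment.** It claims blinding for researchers and analysts only. Data management treats data collectors as a separate group, whose code records researchers cannot access. The fault is an omission in Masking, not a false statement.
- **That the same person who disclosed the arm returns at T1.** Data collectors appear in the plural, and nothing says who makes which visit. Only the role is the same.
- **That only intervention families choose the setting of data-collector visits.** Study setting does say: "Families in the intervention group have the choice of having the ACP conversations and visits from the data collector at home". This is one loose sentence. No arms exist at baseline, and Data collection procedures makes no distinction by arm.
- **That the change of mode at T2 biases the results.** It applies to both arms, and Data analysis compares arms at each time point with baseline adjustment. No analysis of change from T1 to T2 is planned.
- **That the satisfaction items contaminate the PACS.** Their position in the T1 questionnaire is not shown, and Table 3 lists the PACS first.

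**Conclusion.** The point holds in limited form. At T1 the primary score is taken by interview by the role that also discloses allocation. No safeguard is described, and Masking is silent on the role. This adds an avoidable source of bias, probably in favour of the intervention, to the response bias that cannot be avoided.

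Its size cannot be derived from the documents. The false-positive range of about 7% to 36% rests wholly on an assumed shift of 1 to 4 points, the planning SD of 11.4, 43 completers per arm and an unadjusted two-sided t-test. It shows that a modest shift would matter and is not a forecast.

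No stated figure in the plan is wrong. This is a worthwhile low-cost improvement and not a defect that invalidates the design. It is best made before further T1 data are collected, because bias that enters at collection cannot be removed by analysis.

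**What to change.** 1. **Separate the tasks.** Have allocation disclosed and booklets delivered by post, or by someone who does not take the T1 PACS. Reconcile Table 2 with the list of key components on how booklets reach families.
2. **Preferred: keep the interview and remove knowledge of the arm.** Assign the T1 interview to a data collector who is not told the allocation and who asks the family at the start not to reveal it. T0 and T1 then keep the same mode.
3. **Alternative: self-completion at T1.** The adolescent completes the PACS alone, online or on paper, apart from the parents, with the data collector giving practical help only. The downside is a T0 to T1 mode difference for families already enrolled, equal in both arms.
4. **Order of items.** Ask the intervention-only satisfaction items after the PACS, so that they cannot reveal the arm before the primary score is recorded.
5. **Masking section.** State whether data collectors are blind at T1. If they cannot be, say so and list it as a limitation.

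The cost is a change in procedure wording and a reallocation of tasks among existing staff. Sample size, endpoint and analysis model are unchanged. Some response bias will remain because adolescents know their arm.
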